**Fig 3. Study Design and Procedure**

*The upper portion indicates the overall study design. The middle portion indicates the timeline for assessment of scales and EEG at baseline and post-intervention, also follow-up time-points. Brief mindfulness and relaxation training was administered to intervention group and control group after recruitment.Baseline assessment (-T2, -T1) was finished before intervention. Audio guidance was delivered for everyday's practice for BMT group. There is no other practice and intervention for control group after training. The lower portion indicates modules of psychological and behavioral assessments during the baseline and 5 follow-up sessions. Executive function measurement was implemented via EEG tasks including Stroop, More-odd Shifting, N-back. INT: intervention, INST:monthly intensive training (red triangle); rs-EEG: resting-state EEG; BMT: brief mindfulness training; VAS: Visual analogue scale; SMT: state-mindfulness.*

1. ***Sample size estimation. [List the four elements: δ(Δ) or π1, π2, α, β or Power, and provide the calculation formula]***

In this trial, Stroop reaction time related to executive function will be used as the primary indicator, and the sample size estimation will be conducted using the pwr package in R software. It is set that δ(Δ)tot = 125, corresponding to an expected reduction of 125ms in reaction time for the experimental group after the intervention. Additionally, α is defined as 0.05 and β as 0.80.

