The estimation of Cohen's d is required, with the formula Cohen's d = (δ(Δ) / SDestimate). Referencing studies in similar populations [<https://www.ncbi.nlm.nih.gov/pmc/articles/PMC8939409/>], SDestimate is taken as 250. Therefore, the relevant command is pwr.t.test (d = cohen_d, sig.level = 0.05, power = 0.80, type = "paired", alternative = "two.sided"), resulting in a sample size estimate of 34. Thus, the estimated sample size for the experimental group should be no less than 34 individuals; considering a natural dropout rate of 20%, the sample size for the experimental group should be at least 41 individuals. A ratio of 2:1 will be used to include 20 recreational gamers in the intervention group. A total of 61 participants are required for the intervention group. In order to maintain appropriate comparability, we will recruit an additional 61 participants with matching demographic profiles and equivalent levels of IGD (Internet Gaming Disorder) severity for the control group. Thus, the study demands a cumulative participation of 122 individuals in total.

1. ***Methods of randomization and concealed allocation. [Randomization is used to reduce the risk of selection bias. Methods for generating random number sequences include computer software, random number tables, semi-random or pseudo-random methods (such as using dates, birthdays, or even/odd numbers of hospital visits). Please describe the individuals involved in generating random number sequences and the methods they use. Concealed allocation is used in treatment studies to reduce the risk of selection bias. Key steps in concealed allocation include having a designated person determine the allocation sequence, ensuring that this person is not involved in enrolling participants, and securely storing the allocation table. Please provide detailed descriptions of these steps. Central randomization is a robust method of concealed allocation. Describe the individuals and methods involved in determining the allocation sequence]***

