(1) Primary indicators: average daily gaming time (self-reported by participants), Five Facet Mindfulness Questionnaire (FFMQ), Internet Addiction Test (IAT), Game Craving Scale (adapted from QSU-Brief), Adolescent Executive Functioning Scale (EFS-A), Barratt Impulsiveness Scale, State Mindfulness Scale, Game Craving Visual Analogue Scale, behavioral data, and EEG data (from EEG equipment).

(2) Secondary indicators: Self-Rated Sleep Status Scale, Depression-Anxiety-Stress Scale (DASS-21), Positive and Negative Affect Schedule (PANAS).

(3) Safety indicators: Researchers will inquire daily during the intervention period whether participants experience any adverse reactions. If there are any adverse reactions, they will communicate in person or by phone with the research staff.

Measurement time points are detailed in item 5.

1. ***Definition of Participant Effectiveness Determination. [This includes definitions for participant withdrawal, exclusion, loss to follow-up, confounding factors, study discontinuation, and study suspension]***

(1) Participant Withdrawal: Each participant can withdraw from the study at any time during the experiment without providing any reason. Participants who withdraw voluntarily will not be included in the analysis. Under the conditions of a mixed study, we have a complete access procedure for withdrawn participants. If participants are willing to provide a reason for their withdrawal, it will be recorded by the researchers.

(2) Participant Exclusion: If participants cannot consistently participate in the group interventions during the training process—where the focused breathing meditation training lasts one week—those who attend fewer than 5 sessions will be considered not fully intervened and should theoretically be excluded or adjusted using a mixed-effects model.

(3) Participant Loss to Follow-up: If any participant cannot be contacted for two consecutive attempts after the intervention is completed, they will be classified as lost to follow-up.

(4) Participant Contamination: After the intervention is completed, we will conduct a census of participants. If any participant in the control group attempts to learn about the training methods of the intervention group (or vice versa) and tries to train, they will be classified as contaminated participants.

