| **Table 1. Evaluated variables**   \| **Variables** \| \| **Measures** \| **Timepoints** \| \| --- \| --- \| --- \| --- \| \| **Primary outcome** \| **Trait-, State-mindfulness** \| Five Facet Mindfulness Questionnaire (FFMQ) [[6](#_ENREF_6" \o "Baer, 2006 #537)] \| -T2, -T1; T0, T1, T2, T3, T4, T5 \| \| State Mindfulness Scale [[7](#_ENREF_7" \o "Yu, 2021 #565)] \| \| **Electroencephalographic (EEG) and behavioral data** \| Behavioral and Electroencephalogram (EEG) data \| \| Heart Rate Variability \| \| **Gaming craving-related metrics** \| Average daily gaming time (self-recorded by participant) \| \| Internet Addiction Test (IAT) [[8](#_ENREF_8" \o "Wang, 2019 #706), [9](#_ENREF_9" \o "Young, 1998 #711)] \| \| Gaming Craving Visual Analogue Scale [[10](#_ENREF_10" \o "Ko, 2013 #65)] \| \| Gaming Craving Short Questionnaire (adapted from QSU-Brief) [[11](#_ENREF_11" \o "Cox, 2001 #543)] \| \| **Impulsivity** \| Barratt Impulsiveness Scale [[12](#_ENREF_12" \o "Patton, 1995 #547)] \| \| **Executive function** \| Adolescent Executive Functioning Scale (EFS-A) [[13](#_ENREF_13" \o "Huang, 2014 #707)] \| \| **Secondary outcome** \| **Sleep status** \| Self-Rating Scale of Sleep (SRSS)[[14](#_ENREF_14" \o "Li, 2012 #708)] \| -T2, -T1; T0, T1, T2, T3, T4, T5 \| \| **Affect, Stress** \| Depression Anxiety Stress Scales (DASS-21) [[15](#_ENREF_15" \o "Gong, 2010 #709)] \| \| Positive and Negative Affect Schedule (PANAS) [[16](#_ENREF_16" \o "Watson, 1988 #71)] \| \| **others** \| **Socio-demographic and clinical information** \| Demographics including name, gender, handedness [[17](#_ENREF_17" \o "Edlin, 2015 #541)], gaming history duration, average weekly gaming time, psychiatric diagnosis or history of mental health problems \| -T1 \| \| **Psychological status** \| Patient Health Questionnaire-9 (PHQ-9) [[18](#_ENREF_18" \o "Kroenke, 2001 #73)] \| \| Generalized Anxiety Disorder-7 (GAD-7) [[19](#_ENREF_19" \o "Spitzer, 2006 #544), [20](#_ENREF_20" \o "shan, 2015 #546)] \| \| **Presence of IGD** \| Diagnostic and Statistical Manual of Mental Disorders, Fifth Edition (DSM-5) nine diagnostic criteria [[21](#_ENREF_21" \o "Petry, 2014 #76)] \| \| Gaming history, average weekly gaming time \| \| **Personal traits** \| Chinese Big Five Personality Questionnaire [[22](#_ENREF_22" \o "Wang, 2011 #710)], attachment style [[23](#_ENREF_23" \o "Li, 2006 #702)], self-compassion [[24](#_ENREF_24" \o "Kong, 2021 #703)] \| |

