For power spectrum and functional connectivity analysis: EEG data will calculate the relative power of six EEG frequency bands at the single electrode and ROI levels (δ: 1-4Hz, θ: 4-8Hz, α: 8-13Hz, low β: 13-20Hz, high β: 20-30Hz, low γ: 30-48Hz). Phase Locking Value (PLV) and Phase Lag Index (PLI) will be calculated using the FieldTrip toolbox. Source localization analysis will be used to explore functional changes in subcortical regions.

For ERP data, we selected the N2 and P3 components based on previous research. The analysis epoch will be 1000ms, with the baseline being the 200ms before stimulus presentation. The N2 negative component is primarily induced by the frontal central region, so the frontal midline electrodes were chosen as the region of interest. The time window for N2 is 250-350ms post-stimulus lock, while P3 is a positive component appearing in the parietal mid/post region, with the parietal electrodes selected as the region of interest, and the time window is 300-400ms post-stimulus presentation. To avoid Type I error rates, we did not analyze individual electrodes; instead, we averaged the amplitude values of the electrodes within the selected time window as the dependent variable for analysis. All work related to ERP component analysis was conducted using ERPLAB.

Finally, we will simultaneously conduct ITT analysis for this study, considering dropout levels as a very important indicator for recording and analysis, attempting to objectively reveal the intervention effects of focused breathing meditation training on executive function from both ITT and PP analysis perspectives..

1. ***Participant management system.***

(1) Contact and Guidance: A contact group composed of relevant researchers is responsible for providing guidance or answers to all research-related content or questions encountered by participants throughout the duration of the study. This ensures that participants have a sufficient understanding of the research and can better cooperate with the process. Researchers must promptly address and record any instances of withdrawal, removal, loss to follow-up, termination, or suspension involving participants.

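### The sample size rests on Stroop reaction time as the single primary outcome, but the outcome list and Table 1 give ten or eleven unranked primaries, do not name it, and mark no primary visit

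*Protocol*

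**What the plan says.** Three places in the protocol define the primary outcome, and they differ.

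- **Sample size estimation.** "Stroop reaction time related to executive function will be used as the primary indicator". The effect is a fall of 125 ms, "corresponding to an expected reduction of 125ms in reaction time for the experimental group after the intervention", and "SDestimate is taken as 250". The calculation is one paired, two-sided t-test at 0.05 with power 0.80, giving 34, raised to 41 for dropout.
- **Outcome Measures.** A list of ten that begins "Primary indicators: average daily gaming time (self-reported by participants), Five Facet Mindfulness Questionnaire (FFMQ), Internet Addiction Test (IAT), Game Craving Scale" and continues with the executive function scale, the Barratt scale, the State Mindfulness Scale, the craving visual analogue scale, behavioural data and EEG data. Stroop is not named.
- **Table 1.** Much the same measures under the primary heading, plus "Heart Rate Variability". Every one is assigned to both baseline visits and to T0 through T5. Stroop is again not named, and no visit is singled out.

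The Fig 3 caption says that executive function is measured by the Stroop, More-odd Shifting and N-back tasks. Stroop reaction time is therefore one of several results inside the behavioural data item. The EEG item is broader still. Under Statistical analysis methods, "EEG data will calculate the relative power of six EEG frequency bands at the single electrode and ROI levels", and phase-locking value, phase lag index, source localization, N2 and P3 follow. The only remark on Type I error there concerns averaging electrodes for the ERP components.

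**The concern.** A trial sized on one test at 5% controls error at 5% only if that test is the one on which the claim rests. Here the section that defines outcomes does not single that test out. It places ten or eleven measures on an equal footing, some of them families of results, and gives none a leading visit. Someone writing the report could take the primary outcome to be Stroop reaction time after training, the Internet Addiction Test at one year, or an EEG feature, and cite the protocol for each.

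The Study design section states a superiority aim, so the trial is not framed as purely exploratory. The protocol also says that the trial has not started. A primary outcome named now is credible; one named after the data are seen is not.

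**Working it through.** **1. The protocol's own figure.** Inputs from Sample size estimation: δ = 125 ms, SD = 250 ms, two-sided α = 0.05, power 0.80 (the text labels this β), paired t-test.

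- d = 125 / 250 = 0.5.
- Exact noncentral-t solution: n = 33.37, rounded up to 34. The stated 34 reproduces.
- 34 × 1.2 = 40.8, rounded up to 41, also as stated.

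So 34 rests on a single endpoint, tested once at the full 5%, as a change within the experimental arm.

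**2. Counting the listed primaries.**

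- Outcome Measures: 10 items.
- Table 1: 10 rows, or 11 measures if behavioural and EEG data are counted separately.
- Post-baseline visits: T0 plus T1 to T5 = 6.
- Measure-by-visit pairs: 10 × 6 = 60, or 11 × 6 = 66.

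**3. Illustrative chance of at least one false positive.** Assume one unadjusted 5% test per item, with no true effects. If independent, the chance is 1 − 0.95^k. For correlated tests, assume equicorrelated normal statistics with common correlation r. The protocol gives no correlations, so a range is shown.

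| Tests k | Independent | r = 0.3 | r = 0.5 | r = 0.7 | r = 0.9 |
| --- | --- | --- | --- | --- | --- |
| 10 | 40% | 35% | 29% | 21% | 13% |
| 11 | 43% | 37% | 30% | 22% | 13% |
| 60 | 95% | 85% | 66% | 43% | 20% |
| 66 | 97% | 87% | 69% | 44% | 21% |

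The randomization section mentions EEG collection explicitly only at baseline and after the intervention. If task, EEG and heart-rate data came only at T0, the counts would be 8 × 6 + 2 = 50 or 8 × 6 + 3 = 51. The independent figures would then be 92–93%. One test per item undercounts the behavioural and EEG items.

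**4. Keeping every listed measure primary.** With Bonferroni, the same paired calculation at α = 0.05/10 needs 58 rather than 34, and at 0.05/60 needs 76. Power at n = 34 falls to about 47% and 25% respectively.

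**5. Power of the single between-arm test that the superiority aim implies.** Assume that d = 0.5 also applies between arms (two-sample t-test, two-sided 0.05).

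- 34 per arm: about 53%.
- 41 per arm, all analysed: about 61%.
- 80% power needs 64 per arm.

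**The case against.** The strongest reply is that the intended test can largely be pieced together. The Study design section gives superiority of mindfulness over control in the IGD population. The objective is executive function. The sample size section picks Stroop reaction time and an effect after the intervention, which points to T0. Stroop also falls within the behavioural data item, so it is unnamed in the primary list but not excluded from it. All of this stands. The hypothesis is not missing; the defect is an unranked list that conflicts with the sample size section.

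A reader might go further and infer that the protocol allows success to be claimed on any of 60 or more tests, with a false-positive chance near 95%. The text does not support that. It declares no success rule and no scheme of one test per measure per visit; it mentions only t-tests, covariance analysis and the like. The 95–97% figure also needs independence between repeated measures on the same people, which is implausible.

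Nor is the absence of a multiplicity procedure a fault here. Testing order, adjustment method and the handling of EEG test families may sit in a statistical analysis plan that is not shown. What such a plan cannot excuse is a protocol that names its primary outcome in conflicting ways.

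**Conclusion.** The point holds as an inconsistency within the protocol and should be fixed before enrolment. One section sizes the trial on a single Stroop test. Two others list ten or eleven primaries over six post-baseline visits, without naming Stroop reaction time or a primary visit.

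The size of the risk depends on assumptions that the protocol does not settle. If each measure were tested once without adjustment, the chance of a false positive would run from about 13% to 43%. If tested at every visit, it would run from about 20% to 97%. The top of each range is independence and the bottom is a common correlation of 0.9. All of these exceed 5%. They show what the wording leaves open and do not describe a declared plan.

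**What to change.** Reconcile Outcome Measures and Table 1 with the sample size section, and carry the change into the registration.

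- **Primary:** Stroop reaction time at T0, mindfulness versus relaxation, in the IGD participants, two-sided 0.05. State which Stroop metric is meant (overall, incongruent or interference), since the present text leaves that choice open.
- **Secondary:** the other listed measures, and Stroop at T1 to T5.
- **Exploratory:** the EEG spectral, connectivity and source analyses.

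The cost is more than relabelling. Fewer outcomes carry a confirmatory claim, and the stated 80% power must be recalculated, because 34 belongs to a within-arm paired test. The between-arm figures above (53% at 34 per arm, 61% at 41) assume d = 0.5 between arms and the same number of IGD participants in each arm.

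Adjusting for the baseline Stroop value, which is already collected, would recover part of the loss. The gain depends on the correlation between baseline and T0, which the protocol does not give. At an assumed 0.5, the variance is multiplied by 0.75, whether 250 ms is a single-visit SD (1 − 0.5² = 0.75) or the SD of change ((1 + 0.5)/2 = 0.75). Then d = 0.5/√0.75 = 0.577, and power is about 65% at 34 per arm and 73% at 41. The sponsor should state the assumed correlation and either accept the resulting power or enlarge the IGD sample.

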**Fig 2. SPIRIT schedule of enrolment, interventions and assessment.**

** Note: -t2, -t1, baseline (complete measurements twice to get average); t0, post-intervention; t1- t5, 1-week, 1-month, 4-month, 6-month,1-year follow-up.*

1. ***Research background. [usually adopting a four-part structure: (1) Overview of the health problem or research question: definition of the health problem, epidemiological data, etiology, natural history of the disease, disease burden, etc.; (2) Scientific hypothesis: mechanism or principle; (3) Clinical application, for example, treatment studies should explain the treatment methods; (4) Necessity of the study based on current evidence, explaining why this study needs to be conducted]***

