(1) In this study, the intervention period focused on breath meditation lasts for one week and serves as a concise mindfulness behavior training. The study will involve a baseline collection of EEG and other relevant data for all participants, a one-week training on the intervention content, collection of post-intervention EEG and other relevant data, and follow-ups (one week, one month, four months, six months, and one year after data collection post-intervention). During the follow-up phase, participants will undergo multiple mindfulness training sessions. Grouping will occur after the baseline data collection for participants is completed.

(2) The breath meditation training is the primary intervention method employed in this study. The design includes grouping into an experimental group and a control group: the experimental group (breath meditation training) and the control group (relaxation training). The recruited participants are from the same school, and their connections make it challenging to implement the criteria for double-blind randomization.

(3) The randomization process for this trial will utilize the random sequence generator available at random.org.

1. ***Blinding. [Blinding is used in treatment studies and diagnostic trials to reduce the risk of implementation bias and measurement bias. Implementing strict confidentiality measures, such as using placebos or simulating procedures, is an effective blinding method. If blinding is necessary and feasible for your study, describe the methods and procedures for implementing blinding]***

This trial involves group therapy, with participants being students from the same school. Therefore, it is possible that among participants who may know each other or even among those who do not, conversations related to the experimental training they are undergoing may arise. Additionally, maintaining blinding for the researchers is quite challenging, as they can easily be influenced by information related to the experiment during the process. As a result, it is not feasible to meet the double-blind requirements of clinical trials.

1. ***Outcome Measures. [Outcome measures are used to evaluate the results of a study and can include primary, secondary, and safety measures, including adverse events and reactions. Please describe the names of the measures, the methods of measurement, and the time points at which they are assessed]***

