| --- | --- | --- | --- | --- | --- | --- | --- | --- | --- | --- | --- | --- | --- | --- | --- | --- | --- | --- | --- | --- | --- | --- | --- | --- | --- | --- | --- | --- | --- | --- | --- | --- | --- | --- | --- | --- | --- | --- | --- | --- |

1. ***Definition, identification methods, and management systems for adverse events and reactions.***

[name] [[25](#_ENREF_25" \o "Farias, 2020 #701)] systematically describes the adverse events and reactions caused by meditation (meditation adverse events, MAEs) in the text, which we categorize as follows:

**Mental MAEs:** The most common include anxiety and depression, while other relatively common issues include psychotic or delusional symptoms, dissociation or depersonalization, fear or phobia, trauma re-experiencing, and suicidal thoughts and behaviors.

**Physical MAEs:** The most common is bodily tension, followed by pain and gastrointestinal issues. Localized pain often involves the abdomen/stomach and neck. Most physical MAEs are based on patient self-reports; however, some variables also used physiological and biological measurement methods, such as heart rate, blood pressure, skin conductance, and cortisol levels (it is not possible to rule out that these physiological measuring methods might cause side effects).

**Neurological/Cognitive MAEs:** The most common are abnormal cognitive experiences, including thought disorganization, forgetfulness, sensory hypersensitivity, and impaired memory reliability. Some patients also experienced involuntary bodily movements and muscle contractions during meditation.

Based on the types of adverse effects mentioned above, to address adverse events during the intervention process, we have included relevant adverse reaction feedback questions in the weekly follow-up questionnaires. The experimental group will conduct weekly monitoring; after collecting the questionnaires, if an adverse event feedback option is marked "yes," the relevant person in charge from the medical school and psychology department will be responsible for communicating with the subjects, assessing their psychological and physiological conditions, and gauging the subjects' willingness. After a tripartite consensus (medical school, psychology department, and the individual subject), they will decide whether the subjects experiencing adverse events can participate in subsequent research.

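### Harm collection after the one-week intervention is unscheduled and inconsistently described, although mindfulness training continues into follow-up

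*Protocol*

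**What the plan says.** The protocol describes harm collection in two places.

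- **Outcome Measures, item (3), safety indicators:** "Researchers will inquire daily during the intervention period whether participants experience any adverse reactions". Under Methods of randomization, item (1), "the intervention period focused on breath meditation lasts for one week".
- **The section on definition, identification and management of adverse events:** "we have included relevant adverse reaction feedback questions in the weekly follow-up questionnaires". The stated purpose is "to address adverse events during the intervention process". The section adds: "The experimental group will conduct weekly monitoring". It gives neither a first nor a last week.

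The visit schedule, in the note to the SPIRIT schedule, is "t1- t5, 1-week, 1-month, 4-month, 6-month,1-year follow-up". The SPIRIT table has rows for demographics, primary outcomes, secondary outcomes and daily records, but none for adverse events. Table 1 lists the measures and their time points and has no adverse-event item.

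Training does not end with the intervention week. Methods of randomization, item (1), says: "During the follow-up phase, participants will undergo multiple mindfulness training sessions". The Fig 3 legend defines a marker as "INST:monthly intensive training (red triangle". The Standard operating procedures also plan several sessions in follow-up, with on-site check-ins by researchers, and have each day's material sent to participants so that they can keep practising. According to the Fig 3 legend, the control group has no further practice after its training.

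**The concern.** One section ties harm inquiry to a single week. The other relies on a questionnaire that appears nowhere in the schedule. A study team working from the SPIRIT table and Table 1 would find no adverse-event item to administer at any visit from T0 to T5, although mindfulness training continues for the experimental group.

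Two things are at stake. The first is detection. The adverse-event section itself lists serious psychological reactions as possible harms of meditation, and the protocol makes any adverse event a ground for considering termination. That rule can act only on events that come to light. The second is reporting. If teams read the text differently, or ask one arm more often than the other, the final safety statement will have no defined observation window and no clear denominator.

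**Working it through.** The plan gives no figure for harm collection, so there is none to reproduce. The check sets the sections side by side and adds simple calendar arithmetic.

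**1. What each place provides**

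| Place in protocol | Adverse-event inquiry | Window |
|---|---|---|
| Outcome Measures, item (3) | Daily, by researchers | Intervention period (1 week) |
| Adverse-event section | Questions in weekly questionnaires; experimental group named | Not stated |
| SPIRIT table and note | No row | t0, then 1 week, 1, 4, 6 and 12 months |
| Table 1 | No item | T0 to T5 for primary and secondary measures |
| Methods of randomization (1), Fig 3 legend, Standard operating procedures | Not mentioned | Training and practice continue into follow-up |

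**2. Two readings of the weekly questionnaires**

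- *They stop with the intervention week.* The stated purpose, which refers to the intervention process, leans this way. Inquiry then ends while training goes on, and calling them follow-up questionnaires makes little sense.
- *They run through follow-up.* The name leans this way. Over one year this means about 52 contacts. The schedule has 5, so about 52 − 5 = 47 are missing from it, and the safety item under Outcome Measures describes only part of the inquiry.

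The text supports neither reading clearly, and the schedule and tables are incomplete under both.

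**3. Gaps between scheduled visits**

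One month is 365.25 / 12 / 7 = 4.35 weeks. Visits therefore fall at about weeks 1, 4.3, 17.4, 26.1 and 52.2 after the intervention.

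- End of intervention to T1: 1 week
- T1 to T2: 4.3 − 1 = 3.3 weeks
- T2 to T3: 17.4 − 4.3, about 13.0 weeks (3 months)
- T3 to T4: 26.1 − 17.4 = 8.7 weeks (2 months)
- T4 to T5: 52.2 − 26.1 = 26.1 weeks (6 months)

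These are the recall periods that would apply if adverse-event questions were asked only at visits.

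**4. Can the affected share of exposure be stated?**

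The number of follow-up sessions, s, is not given. Assume d = 5 to 7 sessions in the intervention week. The protocol treats fewer than 5 attended as not fully intervened; 7 would be one a day. The share of sessions falling in follow-up is s / (s + d):

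| s | d = 7 | d = 5 |
|---|---|---|
| 2 | 2/9 = 22% | 2/7 = 29% |
| 4 | 4/11 = 36% | 4/9 = 44% |
| 8 | 8/15 = 53% | 8/13 = 62% |
| 12 (monthly for a year) | 12/19 = 63% | 12/17 = 71% |

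The share runs from about a fifth to about seven tenths, so no single figure can be drawn from the document.

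**The case against.** The strongest reply is that monitoring in follow-up is planned. The adverse-event section has weekly questions and a review route, and it names the experimental group, which by the Fig 3 legend is the arm that keeps training. With no end date given, the section can be read as covering all of follow-up. Other sources also exist. DASS-21, PANAS and the sleep scale are taken at every visit from T0 to T5. EEG recording stops if a participant reacts badly. The emergency team is charged with identifying adverse reactions during the study. The daily-records row of the SPIRIT table is marked from t0 to t5.

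Much of this stands, and it limits what can be claimed. A reader might infer that most of the exposure has no harm collection, that inquiry covers only 1 of about 53 weeks, that exposure lasts a full year, or that later events surface only if a participant volunteers them. The documents do not support these statements. The first two treat the weekly monitoring as absent when its duration is merely unstated. The session count and the length of continued practice are not given. The sources just listed are partial routes that do not all depend on the participant coming forward. The monthly frequency comes only from the Fig 3 legend; the drawing was not available here, so the number and position of its markers are unknown. The documents also give no data on when such events begin, so nothing can be said about how many would arise after the first week.

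The reply does not remove the inconsistency. The scales are secondary outcomes and do not ask about the physical and cognitive reactions that the protocol lists. The content of the daily records is undefined. The weekly questionnaire still has no place in the schedule and no stated duration.

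**Conclusion.** The point holds as one of scheduling and consistency. After the intervention week, no visit from T0 to T5 carries an adverse-event item in the SPIRIT table or Table 1. The two sections that describe harm inquiry differ in frequency, in window and in whom they name. Training continues meanwhile.

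Whether follow-up exposure is actually uncovered depends on how long the weekly monitoring runs, and the protocol leaves that open. The size can be given only as calendar gaps between visits, from 1 week up to about 6 months, and not as a share of exposure. The conclusion assumes that the SPIRIT table and Table 1 are the operative schedule and that Fig 3 holds no adverse-event item absent from its legend. When and how harms are collected belongs in the protocol and is not a matter to leave to an analysis plan. It should be settled before recruitment, which the protocol says has not begun.

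**What to change.** 1. Reconcile the safety item under Outcome Measures and the adverse-event section with the visit schedule, so that they state one collection window, one frequency and the same participants.
2. Add an adverse-event row to the SPIRIT table and an adverse-event item to Table 1.
3. Put the existing adverse-reaction questions into the T0 to T5 questionnaires for all participants in both arms, asking about the time since the last contact.
4. Ask the same questions at the check-ins that researchers already hold at follow-up training sessions.
5. Keep the weekly questionnaires, and state when they start and end. Deleting them would remove the most explicit harm questions in the plan.

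The cost is an amendment to two tables and two sections, and a few items added to contacts that already take place. No new visit is needed. The weakness is recall, which will be imperfect over the longer gaps, up to about 6 months between T4 and T5. The weekly questionnaires and training check-ins would shorten those gaps wherever they run.
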